## Outcome measurements

### Muscle pain assessment

A VAS will be used to determine the recreational runner’s muscle pain [32].

### Body composition analysis

Before and after the intervention, the body composition of participants will be measured using bioelectrical impedance analysis (Tanita BC-418, Tanita Corp., Tokyo, Japan).

### Anthropometric measurements

To measure the height and weight of participants, a stadiometer will be used (Seca, Hamburg, Germany). The body weight of participants will be measured with a minimum of wearing and without shoes to the nearest 100 g. Height will also be measured at a standing position and barefoot with an accuracy of 0.1 cm. BMI will finally be calculated using the measured weight and height. By dividing weight in kilograms by height squared in meters, BMI will be obtained [37]. Anthropometric measurements will be done twice, before and after the study.

### Aerobic, anaerobic performance

To assess the aerobic performance, the Cooper 12-min run test will be used. The runners will be asked to run as far as possible for 12 min. The covered distance then will be recorded [38]. Furthermore, the running-based anaerobic sprint test (RAST) will be used to assess the anaerobic performance of participants. RAST consists of six 35-m sprints separated by a 10-s recovery period. Each sprint will also be timed [39].

### Laboratory investigations

#### Blood sampling

Blood sampling will be done during three stages; before the intervention, immediately after the last training session on the fourteenth day, and 24 h after the previous training session. A 10-mL blood sample will be obtained during the three stages: before the intervention, immediately after the last training session on the fourteenth day, and 24 h after the last training session by a lab technician. Plasma centrifugation will be carried out at a speed of 1500 RPM for 20 min. Then, the plasma will be collected into separate micro-tubes and placed in a freezer at a temperature of − 70 °C before laboratory analysis.

#### Protocol amendments

Any changes or amendments in protocol will be reviewed by the principal investigator and approved by the other study investigators. Any modifications will be eventually reported.

#### Data collection and management

MN will collect data from questionnaires. After completion of the questionnaires, MN will assess the collected data and, if there were any discrepancies in answers, the questioner will be requested to answer more clearly to reduce bias.

#### Statistical analysis

Statistical analysis will be done using SPSS version-24 software (SPSS, Inc. Chicago, IL, USA). Regarding the missing values, the data analysis will be subjected to intention-to-treat (ITT) analysis. We will use the multiple imputation approach to perform ITT. The Kolmogorov-Smirnov test and Q–Q plot will be used to examine the normal distribution of variables. In order to compare the baseline value of quantitative and qualitative variables, the *t*-test and chi-square test will be used. To determine the change of variables at baseline and after the intervention, the paired sample *t*-test will be conducted. The mean change of the placebo and intervention group variables will also be compared using an analysis of covariances after adjusting the confounding variables. Mann-Whitney test will be used for quantitative non-normal variables. In order to compare the mean changes of the baseline and end of the trial, the paired-sample *t*-test and Wilcoxon test will be used for normal and non-normal data, respectively. Regarding repeated measured variables (three-time measurements), a two-way analysis of variance (ANOVA) with the Sidak post-hoc test will be applied to assess the time × group interactions. Also, the Mauchly sphericity test will be used to determine data homogeneity; in presence of a violation, the Greenhouse-Geisser adjustment will be used. *P* < 0.05 will be considered statistically significant in all tests. Furthermore, it is notable that in the case of non-normally distributed data, we will do Log transformations.

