### Randomization and blinding

The recreational runners meeting the inclusion criteria will be randomized to receive either the TT (*n* = 17) or the maltodextrin capsules (*n* = 17). Randomizations will be conducted using random allocation software (RAS) via randomization blocks (Version 2.0, for Windows, Isfahan, Iran) [30]. After enrolling participants, they will be stratified into different blocks based on their VO_2max_ and gender distribution and then will be allocated to the intervention or control groups in random order. Using RAS, a random allocation sequence will be generated. Then, a third individual who is unaware of the study's aim will use computer-generated random sequences to allocate participants into TT and placebo groups.

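### Randomisation is stratified by VO2max and gender, but no planned between-group analysis names either factor, and the ANCOVA covariates are left as unnamed confounders

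*Protocol article*

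**What the plan says.** Protocol article, Randomization and blinding: once enrolled, participants are not allocated in one list; "they will be stratified into different blocks based on their VO_2max_ and gender distribution", and are then allocated to the arms.

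Protocol article, Statistical analysis, gives three between-group methods:

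- **ANCOVA.** Mean changes are "compared using an analysis of covariances after adjusting the confounding variables". No covariate is named and no rule for choosing one is given.
- **ANOVA.** For variables measured three times, "a two-way analysis of variance (ANOVA) with the Sidak post-hoc test will be applied to assess the time × group interactions". Blood is drawn at three stages (Blood sampling), so this is the model for the blood markers. They make up 18 of the 21 items listed under Primary objective; the other three are muscle pain, aerobic performance and anaerobic performance. No covariate is mentioned.
- **Rank test.** "Mann-Whitney test will be used for quantitative non-normal variables". This test takes no covariates. The section also plans log transformation for non-normal data, without saying which of the two comes first.

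The same section plans significance tests between the arms at baseline: "In order to compare the baseline value of quantitative and qualitative variables, the *t*-test and chi-square test will be used". It does not link these tests to the ANCOVA.

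**The concern.** Stratifying makes the arms alike on VO2max and gender. That removes these factors from the true variability of the treatment difference. A model without them still counts their variance as noise, so its standard error is too large and its test rejects too rarely. The precision bought by stratifying is then not used.

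Calling the ANCOVA covariates confounders adds a second problem. Under randomisation a baseline difference between arms is chance, so covariates should be chosen because they predict the outcome, and fixed beforehand. An unnamed list can be settled after the data are seen, and that can push the error rate the other way. The outcome's own baseline value, usually the strongest predictor, is not named either.

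**Working it through.** **1. The plan's own figure.** Sample size section: difference 1128.4 U/L, SD 871.05 U/L, 95% confidence, 90% power, 15% drop-out. Standardised effect = 1128.4 / 871.05 = 1.30. A two-sided t-test at 5% has power 0.886 with 13 per arm and 0.910 with 14, so 14 are needed; 14 / 0.85 = 16.5, rounded up to 17. The stated 17 per arm reproduces, and this point does not affect it.

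**2. Leaving the strata out.** The documents do not say how much outcome variance the strata explain, so R² is an assumption, taken over a range. With outcome SD 1 and N = 34, a model without strata reports a standard error near √(4/34) = 0.343. With the strata in, it is near √(4(1 − R²)/34). The ratio is 1/√(1 − R²): 1.05, 1.20 and 1.41 at R² = 0.1, 0.3 and 0.5.

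Simulation check: 8,000 runs per setting, 34 participants, two binary strata factors, blocks of two, least squares with and without the factors.

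| R² | SE, strata out | SE, strata in | Ratio | True SD of estimate, strata out | Type I error, out | Type I error, in |
|---|---|---|---|---|---|---|
| 0 | 0.340 | 0.341 | 1.00 | 0.338 | 4.7% | 4.8% |
| 0.1 | 0.341 | 0.324 | 1.05 | 0.329 | 4.5% | 5.4% |
| 0.3 | 0.343 | 0.286 | 1.20 | 0.293 | 2.1% | 5.1% |
| 0.5 | 0.343 | 0.240 | 1.43 | 0.248 | 0.8% | 4.4% |

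**3. Power, strata out versus in.** The first row comes from the same simulation. The other two use four strata of 8, 16 per arm, with 5,000 runs per setting at 1 SD and 3,000 at 1.30 SD.

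| True effect | R² values | Power, out vs in |
|---|---|---|
| 0.8 SD (illustrative) | 0, 0.1, 0.3, 0.5 | 60 vs 60, 63 vs 66, 63 vs 77, 64 vs 89% |
| 1 SD (illustrative) | 0.1, 0.2, 0.3, 0.4 | 80 vs 83, 80 vs 86, 82 vs 90, 83 vs 94% |
| 1.30 SD (planned, CK) | 0.1, 0.2, 0.3, 0.4 | 95.6 vs 96.4, 96.0 vs 97.8, 96.8 vs 98.9, 97.5 vs 99.2% |

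The gain at the planned effect is about 1 to 2 points.

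**4. Choosing covariates from the data.** 3,000 runs per setting, 17 per arm, no true effect, R² = 0.1, 0.3, 0.5 spread over the candidate covariates.

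- Trying every set of up to two covariates and keeping the smallest p-value gives type I error of 7.8, 9.9 and 13.7% with 3 candidates, and 10.6, 12.5 and 15.6% with 5.
- A fixed rule that adjusts only for covariates with baseline p < 0.05 gives 3.9 to 4.7%.

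**5. What R² means for the blood markers.** These simulations compare one value per person. The time × group test compares changes within person, so a stratum effect that is constant over time cancels out. For that test, R² is the share of variance in *change* that the strata explain. This is why the repair below needs covariate-by-time terms.

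**The case against.** The strongest case against is that only a condensed article is at hand, and a covariate list is what a full protocol or analysis plan normally holds. For the ANCOVA list on its own, that stands. It does not cover the ANOVA and the Mann-Whitney test, which the article does state and which have no place for the strata as described.

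It can also be said that comparing mean changes already uses the baseline. It does, but with the coefficient fixed at 1; entering the baseline as a covariate lets the data set the coefficient.

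The size is open to challenge as well. R² has no basis in the documents and would have to hold for changes in many different markers. At the effect used for the sample size, little power is at stake. Both objections are right, and they limit the conclusion.

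Four stronger readings are tempting, and the documents do not support them:

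- *That the ANCOVA leaves out gender and VO2max.* It does not name them, but its wording does not exclude them.
- *That the baseline tests select the covariates.* The text lists both and never connects them.
- *That the error rate is therefore invalid.* The fixed baseline-test rule did not inflate type I error in step 4; inflation needs an analyst to try several covariate sets and keep the best.
- *That diet or activity measured after randomisation will be adjusted for.* The Questionnaires section gives the repeated dietary records another purpose, checking that participants kept to their usual diet.

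**Conclusion.** The point holds in a limited form. Allocation is stratified on two factors that no stated between-group analysis names, and two of the three methods have no covariates at all. If the strata predict the outcome (for the blood markers, its change) and are left out, the tests are conservative: for R² from 0.1 to 0.5, standard errors are about 5 to 43% larger than with the strata, and type I error is about 4.5 to 0.8% instead of 5%. If R² is 0, nothing is lost. The power at stake is about 1 to 2 points for CK at 1.30 SD, but about 4 to 25 points at an illustrative 0.8 SD, so it matters mainly for outcomes with smaller effects than the one used for planning. The open covariate list is a separate weakness: it permits a data-driven choice, though the article does not plan one. This should be corrected, but it does not undermine the design or the sample size.

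**What to change.** State in Statistical analysis that every between-group comparison adjusts for the outcome's baseline value, gender and VO2max (continuous, or in the categories used for stratification), with no other covariate in the main analysis and none measured after randomisation. This fixed list replaces the reference to confounders. In addition:

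- **Three-time markers:** model the two post-baseline values with group, time and group × time, plus the three covariates and their interactions with time, in place of the unadjusted two-way ANOVA.
- **Non-normal outcomes:** log-transform where needed and keep the adjusted model as the main test, instead of Mann-Whitney.
- **Baseline tests:** do not use them to choose covariates; a descriptive baseline table is enough.

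The cost is a few sentences and about 3 degrees of freedom: with all 34 analysed at one time point, 34 − 2 = 32 residual degrees of freedom become 29. Baseline values and stratification factors are already collected, and the sample size does not change. If the strata prove not to be prognostic, the loss is negligible (standard error 0.341 instead of 0.340 in step 2).

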### Sample size

The sample size was estimated using PASS software (version 15) based on CK changes as the primary outcome of the Ma *et al.* study. Considering the mean difference of 1128.4 units of enzyme activity per liter (U/L) between the two groups and also the SDs average of 871.05 U/L, the sample size was calculated [24]. A total of 17 recreational runners were calculated to be involved in each group with a 95% confidence level, a power of 90%, and considering the additional drop-out rate of 15%.

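### CK and the other three-sample markers: the sample size powers one two-group difference, but the analysis tests a 2-df interaction plus an unranked, untimed ANCOVA of change

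*Protocol article*

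**What the plan says.** All references are to the protocol article.

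- **Sample size.** The calculation is "based on CK changes as the primary outcome" of an earlier study, with a "mean difference of 1128.4 units of enzyme activity per liter (U/L) between the two groups" and "the SDs average of 871.05 U/L". With 90% power, 95% confidence and 15% drop-out it arrives at 17 per group. It gives no sampling time, number of repeated measurements or within-person correlation.
- **Abstract and Blood sampling.** CK is among the markers measured in three samples: one before the intervention, and two described as "immediately after the last training session on the fourteenth day, and 24 h after the last training session by a lab technician".
- **Statistical analysis, three-time variables.** For these, "a two-way analysis of variance (ANOVA) with the Sidak post-hoc test will be applied to assess the time × group interactions", with a Greenhouse-Geisser adjustment if sphericity fails.
- **Statistical analysis, change.** "The mean change of the placebo and intervention group variables will also be compared using an analysis of covariances", adjusted for confounders. The sentence is not restricted to variables measured twice and does not say which post-exercise sample defines the change.
- **Significance rule.** Every test is judged at 0.05. None is named as deciding for CK or any other marker.

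**The concern.** CK is the outcome that justifies 34 participants, and that justification rests on one comparison of two means. The analysis assigned to CK is a different test. With three times and two arms, the interaction has (3 − 1)(2 − 1) = 2 degrees of freedom. It asks whether the two time profiles differ in any way, and it uses the pre-treatment value as one of the responses, although treatment cannot have affected it. The comparison closest to the one that was powered, the ANCOVA of change, stands beside it with no stated sample and no rank.

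Two things are at stake. First, a reader of the results could not tell which test and which sample decide for a marker, so a favourable one could be picked after the data are seen. Second, part of the power bought by the sample size can be lost in the omnibus test under some effect profiles.

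**Working it through.** **1. Reproduce the stated sample size.** Difference 1128.4, SD 871.05, so the standardised difference is 1128.4 / 871.05 = 1.295. The article does not state sidedness; two-sided 0.05 is assumed.

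- Normal approximation: n = 2 × (1.960 + 1.282)² / 1.295² = 12.5, so 13 per arm.
- Noncentral t: 13 per arm gives power 0.887 and 14 gives 0.910, so 14 per arm.
- Drop-out: 14 / 0.85 = 16.5, so 17 per arm, as stated. 14 × 1.15 = 16.1 also rounds up to 17.

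The planned number is therefore that of a 1-df two-sample comparison.

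**2. Power of the interaction.** The article gives no correlation, so compound symmetry is assumed with within-person correlation ρ of 0.3, 0.5 and 0.7. The SD of change is set to 871.05; the article calls this figure only an average of SDs. With group differences δ₁, δ₂, δ₃ at the three times, the noncentrality of the 2-df interaction is

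λ = n × Σ(δₜ − mean δ)² / SD²(change), on 2 and 2(2n − 2) df.

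Under these assumptions λ does not depend on ρ. With n = 14, the df are 2 and 52, and (1128.4 / 871.05)² = 1.678.

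| Difference: baseline, immediate, 24 h | Σ(δₜ − mean δ)² in units of 1128.4² | λ | Power by formula | Power simulated |
|---|---|---|---|---|
| 0, full, full | 0.667 | 14 × 0.667 × 1.678 = 15.7 | 0.94 | 0.93–0.94 |
| 0, 0, full (or 0, full, 0) | 0.667 | 15.7 | 0.94 | 0.93–0.94 |
| 0, half, full | 0.500 | 14 × 0.500 × 1.678 = 11.7 | 0.86 | 0.84–0.86 |

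With all 17 per arm, simulated power is about 0.975 for the first two profiles and about 0.92 for the third.

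**3. Power of a single comparison, 14 per arm.**

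- t-test on change at the sample with the full effect: 0.91.
- Baseline-adjusted contrast at that sample: the residual SD is 871.05 × √((1 + ρ)/2), which is 702, 754 and 803 U/L for ρ = 0.3, 0.5 and 0.7. Simulated power is about 0.98, 0.96 and 0.94 respectively, and 0.93 to 0.98 over all runs.

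**4. False-positive chance per marker, no treatment effect.** Simulated at the same three correlations:

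| Reading of the plan | P(at least one between-group test < 0.05) |
|---|---|
| Interaction only | about 0.05 |
| Interaction, or ANCOVA at one post-exercise sample | about 0.08 |
| Interaction, or ANCOVA at either post-exercise sample | about 0.11 (0.10 to 0.12 across runs) |

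Independent tests would give 1 − 0.95² = 0.0975 for two and 1 − 0.95³ = 0.143 for three. The simulated values are lower because the tests share data.

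**The case against.** The strongest reply is that the section assigns tests by type of variable: ANCOVA of change for what is measured before and after (body composition, anthropometry, performance, muscle pain), and ANOVA for the three-sample markers. Each marker then has one omnibus test at about 5%, followed by Sidak comparisons. This is a natural reading, and it is why the error rate has to be given as a range. But the ANCOVA sentence carries no such limit. Even if it did, CK would then be decided only by a test the sample size was not built on, still with no deciding sample. Sidak adjusts the pairs within the ANOVA; it does not cover a choice between ANOVA and ANCOVA.

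It can also be said that detail belongs in an analysis plan that is not shown. That is true of detail, but here the article itself fixes the tests, and what it fixes does not line up with its own sample size.

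A reader might infer more, and the documents do not support it:

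- **That the error rate per marker is doubled.** This needs two ANCOVAs per marker. The section describes a single change from baseline to the end and never plans both.
- **That the trial is underpowered.** The interaction falls below 90% only under the half-effect profile with 14 per arm, and that profile is an assumption.
- **That a significant interaction cannot be located in time.** The plan provides post-hoc comparisons for this.
- **That the plan's imputation ("We will use the multiple imputation approach to perform ITT") cannot be combined with these tests.** Imputed data sets are complete, and pooling rules for several parameters exist. A sphericity-corrected F is awkward to pool, but how to do so is a detail for an analysis plan.

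**Conclusion.** The point holds as a mismatch and an ambiguity. The trial is sized on one two-group CK difference. The test assigned to CK is a 2-df interaction that includes the pre-treatment sample, and an ANCOVA of change may also apply, with no sample and no rank stated. The false-positive chance per marker is about 5%, 8% or 11%, depending on the reading.

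With 14 evaluable per arm, the interaction has 84 to 94% power, against 93 to 98% for a baseline-adjusted contrast at the sample with the full effect. The contrast is clearly better when the effect builds up between the two post-exercise samples, and about equal or better otherwise. These figures assume normal data, compound symmetry, ρ between 0.3 and 0.7, and 871.05 as the SD of change. The article states none of these, except that 871.05 is its SD figure. Multiplicity across the many primary markers is a separate matter and is not counted here.

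**What to change.** For variables measured three times:

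1. Make one between-group contrast decisive. Take it from an ANCOVA, or from a mixed model of the two post-exercise samples, with baseline value, sex and VO2max stratum as covariates (sex and VO2max are the stratifiers in the Randomization and blinding section).
2. Before unblinding, fix its sample time as the one that matches the source of the CK planning figure. The article does not give that time, so the team must look it up and state it.
3. Report the other post-exercise sample as secondary and the ANOVA interaction as supportive.
4. State that the ANCOVA of change applies only to variables measured twice.

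A mixed model is one way to do this, not a requirement; naming the single contrast is what matters. The sample size stays as it is: one named contrast is what 17 per arm already powers (0.91 with 14 evaluable and 0.956 with 17, by two-sample t-test). The cost is a change of wording, and the Trial status section says the trial has not begun. The downside is that the team must commit to one time point in advance.

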**Methods/design:**

This study is a double-blind, randomized, placebo-controlled trial, which will be conducted among recreational runners of Tabriz stadiums, Iran. Thirty-four recreational runners will be selected, and participants will be assigned randomly to two groups: to receive 500 mg TT supplement or placebo capsules twice daily for 2 weeks. Both groups will do high-intensity interval training (HIIT) workouts during the study. Baseline and post-intervention body composition, muscle pain, and aerobic and anaerobic performance will be assessed. In addition, assessment of malondialdehyde (MDA), total antioxidant capacity (TAC), total oxidant status (TOS), superoxide dismutase (SOD), glutathione peroxidase (GPx), uric acid (UA), 8-iso-prostaglandin F2α (8-iso-PGF2α), protein carbonyl (PC), catalase (CAT), glutathione (GSH), nitric oxide (NO), high-sensitivity C-reactive protein (hs-CRP), interleukin-6 (IL-6), interleukin-10 (IL-10), tumor necrosis factor-alpha (TNF-α), creatine kinase (CK), myoglobin (MYO), lactate dehydrogenase (LDH), insulin-like growth factor-1 (IGF-1) irisin, cortisol, and brain-derived neurotrophic factor (BDNF) will be done during three blood samplings. Changes in oxidative stress, anti/inflammatory biomarkers, and sports performance will be assessed as primary outcomes.

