### Primary objective

The primary objective is to assess the effect of TT supplementation on malondialdehyde (MDA), total antioxidant capacity (TAC), total oxidant status (TOS), superoxide dismutase (SOD), glutathione peroxidase (GPx), uric acid (UA), 8-iso-prostaglandin F2α (8-iso-PGF2α), protein carbonyl (PC), catalase (CAT), glutathione (GSH), nitric oxide (NO), hs-CRP, TNF-α, IL-6, IL-10, CK, LDH, MYO, muscle pain, and the aerobic and anaerobic performance of recreational runners with TT supplementation and high-intensity interval training (HIIT) training.

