## Discussion

The interest in natural supplements to promote athletic performance has increased these days among athletes. Recently, TT supplementation has also been raised in various exercises due to its beneficial consequence, which was seen in strength athletes [24]. In a study on boxers, conducted by Ma *et al.*, it has been indicated that TT lowered IGF-1 binding protein-3 levels, which may improve IGF-1 bioactivity, as well as increasing muscle strength and decreasing post-exercise CK levels when used in conjunction with training [24]. In a recent study pilot study also, Talemi *et al.* showed that TT might be effective in the reduction of CK and LDH following the high-intensity resistance exercise in non-athletes [40]. According to a review done by Zhu *et al.*, it has been shown that the TT has a wide range of healthful properties, including antioxidant activity, anti-inflammatory activity, antitumor activity, antibacterial activity, hepatoprotective activity, anthelmintic and larvicidal activity, anticaries activity, antiaging and memory improvement activity [41]. Also, it is worth mentioning that the chemical constituents of TT including steroidal saponins and flavonoids, which have prominent anti-inflammatory and antiaging activities, were found to be the key contributors to conventional pharmacological activities of TT [41]. TT can promote athletic performance and decrease fatigue due to its antioxidant activity and anti-inflammatory activity; in addition, it has been shown that TT supplementation may result in decreased IGF-1 binding protein-3 levels and increased IGF-1 bioactivity. IGF-1 is the upregulator of muscle growth and muscle strength which leads to muscle hypertrophy, repair of muscle damage, and eventually the promoted athletic performance [24, 42, 43].

To the best of our knowledge, this study will be the first to assess the potential effects of TT on recreational runners. The present protocol is based on a randomized placebo-controlled trial design, which presents the strongest empirical evidence regarding the TT supplementation and determines the causality. Besides, the control over participants’ diet and repeated blood collection in this study will provide more precise details.

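### Twenty-one outcomes share primary status and every test is judged at P < 0.05, so an inert supplement has roughly a 31% to 66% chance of at least one significant primary result

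*Protocol article*

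**What the plan says.** **Primary outcomes.** The Primary objective is one sentence. It opens with the oxidative markers MDA, TAC, TOS and SOD, continues through seven more to nitric oxide, and ends with "hs-CRP, TNF-α, IL-6, IL-10, CK, LDH, MYO, muscle pain, and the aerobic and anaerobic performance of recreational runners". It gives no ranking and no lead outcome. The Abstract (Methods/design) describes a narrower set: "Changes in oxidative stress, anti/inflammatory biomarkers, and sports performance will be assessed as primary outcomes". Muscle-damage enzymes and muscle pain are not in that sentence.

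**Decision rule.** Under Statistical analysis, P < "0.05 will be considered statistically significant in all tests". The same section provides for covariance analysis of change, paired tests within each arm and, for variables measured three times, "a two-way analysis of variance (ANOVA) with the Sidak post-hoc test will be applied to assess the time × group interactions". No adjustment across outcomes is stated.

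**Sample size.** "The sample size was estimated using PASS software (version 15) based on CK changes as the primary outcome". The sentence goes on to attribute that primary outcome to the cited earlier study. The calculation takes a difference of 1128.4 U/L, an average SD of 871.05 U/L, 95% confidence, 90% power and 15% drop-out, and arrives at 17 per group.

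**The concern.** The sample-size section budgets a 5% false-positive risk for one comparison. The analysis section then allows that 5% separately for each of 21 outcomes of equal standing. Nothing says which result decides whether the supplement works, or how many outcomes must agree. A report that led with whichever primary outcome crossed 0.05 would be consistent with the protocol as written, and its error rate would be far above the nominal 5%. At stake is the trial's main conclusion.

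**Working it through.** **1. The plan's own figure.** Standardised difference: 1128.4 / 871.05 = 1.295. A two-sided two-sample t-test at 0.05 with 90% power needs 13.56, so 14 per arm. Allowing for drop-out, 14 / 0.85 = 16.5, so 17. The stated 17 per group is reproduced, for CK alone at an unadjusted 0.05 (two-sided is my assumption).

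**2. Number of primary outcomes.**

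| Domain | Outcomes | Count |
|---|---|---|
| Oxidative | MDA, TAC, TOS, SOD, GPx, UA, 8-iso-PGF2α, PC, CAT, GSH, NO | 11 |
| Inflammatory / anti-inflammatory | hs-CRP, TNF-α, IL-6, IL-10 | 4 |
| Muscle damage | CK, LDH, MYO | 3 |
| Pain | Muscle pain | 1 |
| Performance | Aerobic, anaerobic | 2 |
| **Total (Primary objective)** | | **21** |

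The domains named in the Abstract give 11 + 4 + 2 = 17.

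**3. Chance of at least one false positive**, with one two-sided between-arm test per outcome and no true effect.

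- Independent outcomes: 1 − 0.95^21 = 0.659. Expected number of false positives: 21 × 0.05 = 1.05.
- Abstract's set, independent: 1 − 0.95^17 = 0.582.
- Correlated outcomes: simulation of 21 equally correlated normal outcomes, t-tests, 17 per arm, 40,000 runs. The correlations are assumptions.

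| Common correlation | Chance of at least one P < 0.05 |
|---|---|
| 0 | 66% |
| 0.2 | 61% |
| 0.3 | 55% |
| 0.5 | 43% |
| 0.7 | 31% |
| 0.9 | 16% |

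A correlation of 0.9 across enzymes, cytokines, pain and running tests is hard to credit, so I take 0.7 as the upper end. Even there the risk is about six times nominal (31 / 5).

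**4. What the Sidak step covers.** It is a post-hoc test inside the repeated-measures ANOVA of one variable. It adjusts contrasts within that variable and leaves the number of variables untouched.

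**5. What different corrections cost.** Power for the stated CK effect (noncentral t, difference 1.295 SD):

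| Level for CK | 14 per arm | 17 per arm |
|---|---|---|
| 0.05 (single primary, or first in a fixed sequence) | 91% | 96% |
| 0.05 / 4 = 0.0125 (strictest Holm step, four primaries) | 76% | 86% |
| 0.05 / 21 = 0.00238 (Bonferroni over all) | 53% | 68% |

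At 0.00238, 90% power needs 24.6, so 25 completers per arm.

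**The case against.** **66% is the least realistic case.** Several markers plausibly move together: CK with LDH and myoglobin, or TOS with MDA. This stands, and a reader should not take 66% as the trial's error rate. It is not an absolute ceiling either. It is the worst case only for one test per outcome, and the analysis section plans several for many outcomes.

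**The protocol states no rule that one success is enough.** True. A reader might infer that any one of 21 results will be claimed as proof, or that any positive result would carry little evidence. The text supports neither: it gives no success rule at all, and a very small P value for one marker would survive any correction. What remains is that nothing in the protocol prevents a claim built on one result.

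**CK is already the primary outcome, because the trial is sized on it.** The sample-size sentence can be read that way if it is cut short. In full, it gives CK that role in the earlier study. The Primary objective lists CK among 21 without precedence, and the Abstract's primary domains omit muscle damage. Making CK the sole primary outcome is therefore a choice for the investigators, and it narrows the declared question.

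**An unseen analysis plan may add control.** It may, but the article fixes 0.05 for all tests, so a later adjustment across outcomes would contradict it. This is a stated rule and not merely missing detail.

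**The stated intention to publish all primary and secondary data.** That limits selective reporting. It does not lower the false-positive rate.

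The Discussion's remark that the design "presents the strongest empirical evidence regarding the TT supplementation and determines the causality" concerns randomisation and placebo control. I place no weight on it here.

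**Conclusion.** The point holds. The protocol gives 21 outcomes equal primary status (about 17 on the Abstract's wording) and judges each at 0.05 with no control across them. For an inert supplement, the chance of at least one significant primary result is roughly 31% to 66%. That range assumes one two-sided between-arm test per outcome and a common correlation from 0.7 down to independence. Further tests per outcome would raise it; stronger correlation would lower it. The stated 5% error and 90% power apply to CK alone, which the protocol does not designate as this trial's primary outcome. This should be corrected before the trial reports, because it determines what a positive result means.

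**What to change.** 1. Reconcile the primary outcomes in the Abstract with those in the Primary objective.
2. Before outcome data exist, name one primary between-arm comparison. CK change at one named post-training sample is the natural choice: CK is the only outcome sized, and the stated power is kept. The sample must be named because the Blood sampling section has two after training and the sample-size section names neither.
3. If the investigators want several primaries, use either a prespecified fixed sequence starting with CK, or a short list (for example one per domain) tested with Holm, and restate the power. With four primaries under Holm, CK power at 14 per arm would lie between 76% and 91%.
4. Move the other outcomes to secondary, with estimates and 95% confidence intervals, either Benjamini-Hochberg adjusted or labelled exploratory.
5. Change the blanket 0.05 statement under Statistical analysis to match, and update the registry entry.

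**Cost.** Wording and a registry update; no extra participants or assays. Trial status says the trial has not begun and recruitment is under way, so on that account there is still time. The real price is that the demoted outcomes lose confirmatory status, including the oxidative and performance measures that the Abstract and Main aim emphasise. None of them was sized. Bonferroni over all 21 is not recommended, because it would cut CK power to 53% at 14 per arm.
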